### Study setting

The study will be undertaken at six secondary level care clinics and one tertiary clinic for child weight management. These clinics are limited to children less than 18 years of age and their families. Each clinic uses a different model of care with a combination of face-to-face and group education sessions within a multi-disciplinary team.

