#### Recruitment

Potential participants who meet the inclusion criteria will be identified by the primary investigators at each site. The project officer will approach the potential participants during their clinic visits and provide the patient information sheet and consent form. If the participant has provided written consent to take part in the study, the project officer will administer the parent questionnaire. At the end of the questionnaire, participants will have the option to consent for the one-on-one interviews.

It is anticipated that a total of 140 participants will complete the parent questionnaire. As this is a non-randomised acceptability study, a formal sample size calculation could not be performed. The number of participants was a pragmatic decision based on the number of potential participants from each clinic during the study timeframe. This pragmatic approach to sample size calculations has been used previously [26] and is within the acceptable range for sample sizes for quantitative analysis in mixed-methods approaches [27].

Consenting participants will then be contacted by phone by the project officer to invite them to participate in a one-on-one interview. Maximum variation sampling will be used to ensure a range of ages, severity of obesity and sex of the children attending the weight management clinics and a range of clinicians to ensure we capture a broad spectrum of perspectives and experiences [28]. The interviews will continue until data saturation is reached with no new themes emerging. It is estimated that 50 families will take part in the one-on-one interviews. These numbers are based on previous studies assessing parent views [29–31].

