### Part 4: Efficacy of Services for Children Attending Secondary Weight Management Services

Part 4 is an audit of clinic notes and medical records of data collected routinely as part of standard clinical care for pediatric weight management.

Part 4 will address the following objectives:

Secondary objective: To compare the clinical effectiveness of the different models of care for the management of childhood obesity.

Secondary objectives: To assess the impact of the different pediatric weight management models of care on weight-related behaviors (eating, physical activity and sedentary behaviors).

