#### Participants

All children attending the weight management clinics will be included in part 4 of the study.

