#### Data collection

The Healthy Lifestyle Questionnaire was developed for the collection of routine clinical data. This questionnaire includes selected validated questions from the NSW Population Health Survey [36] and the NSW Schools Physical Activity and Nutrition Survey [37]. The questions include data on participants’ demographics, screen time, moderate to vigorous physical activity per day, water consumption, milk consumption, sugary drink consumption, breakfast consumption, consumption of some specific snacks, fruit and vegetable consumption and sleep time. Clinicians complete a section on the patient’s height, weight and co-morbidities as part of routine clinical care. These data will be collected at baseline and at three and six months.

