#### Data analysis

Data analysis will be performed using appropriate statistical software. Data will be presented descriptively including frequency distributions. Differences in parental and clinician satisfaction between models of care will be examined by comparison of means (continuous data) or Chi-squared (categorical data). Effectiveness of each model of care will be determine by change in BMI z-scores, expressed as a continuous variable and categorical variable (change ≤5% or > 5%), from baseline to 3 and 6 months. Weight changes in children with obesity are associated with change in metabolic outcomes [38]. Predictors of effectiveness, including models of care, eating behaviors and physical activity, will be examined by modelling.

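### The 5% category for change in BMI z-score has no stated direction and, even read as a reduction, sets a bar that rises with baseline severity

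*Protocol article*

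**What the plan says.** The Data analysis section of Part 4 (protocol article) states: "Effectiveness of each model of care will be determine by change in BMI z-scores". The change is to be "expressed as a continuous variable and categorical variable (change ≤5% or > 5" per cent), from baseline to 3 and 6 months. Nothing there or elsewhere in the article says whether the category refers to a reduction, a signed change or the absolute size of a change. As written, the percentage applies to the z-score itself.

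The category serves a between-model comparison. The Part 4 objective is "To compare the clinical effectiveness of the different models of care for the management of childhood obesity". On who is analysed, the Participants section of Part 4 says: "All children attending the weight management clinics will be included in part 4 of the study". No limit on baseline BMI z-score is given. On clinics, Study setting says: "The study will be undertaken at six secondary level care clinics and one tertiary clinic for child weight management". On timing, the Data collection section, which covers clinician-recorded height and weight, says: "These data will be collected at baseline and at three and six months". The Recruitment section of Part 1 describes the study as non-randomised.

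**The concern.** There are two separate problems.

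**Direction.** The classes are separated by the size of a percentage without a sign. If size alone counts, a child whose z-score rises by more than 5% shares a class with one whose z-score falls by more than 5%. If follow-up minus baseline is meant, every child who improves falls in the lower class with the unchanged children. Only a third reading, reduction of more than 5% against everything else, gives a usable measure of effectiveness, and the text leaves the reader to supply it.

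**Scale.** Zero on a BMI z-score is the reference population's centre, not an absence of weight, so a ratio to the baseline value has no fixed meaning. A percentage rule asks for a larger absolute fall from a child who starts higher. In a non-randomised comparison that takes all attenders, part of any difference in category rates between models could then come from baseline severity and not from the care given. Stating the direction does not cure this.

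**Working it through.** The article gives no sample size, expected change or standard deviation for this measure, so there is no figure of its own to reproduce. The 5% cut-off comes from the Part 4 Data analysis section. All baseline z-scores, mean changes and SDs below are assumptions for illustration.

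**1. Direction.** Percentage change = 100 × (follow-up z − baseline z) / baseline z. Take baseline 2.4 and changes of −0.30 and +0.30, which are −12.5% and +12.5%.

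| Reading | Change −0.30 | Change +0.30 |
|---|---|---|
| Absolute size | >5% | >5% |
| Signed (follow-up minus baseline) | ≤5% | >5% |
| Reduction | >5% | ≤5% |

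The three readings give three different classifications of the same two children.

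**2. The bar as a function of baseline.** Required fall = 0.05 × baseline z.

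- z = 1.5: 0.05 × 1.5 = 0.075
- z = 2.0: 0.05 × 2.0 = 0.10
- z = 3.0: 0.05 × 3.0 = 0.15
- z = 3.5: 0.05 × 3.5 = 0.175

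Conversely, one fall of 0.10 is 0.10/1.5 = 6.7% from 1.5, exactly 5.0% from 2.0 and 0.10/3.5 = 2.9% from 3.5. This step needs no distributional assumption.

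**3. Effect on category rates, with a reduction assumed to be meant.** Let the change be normal with the same mean −0.10 and SD 0.20 whatever the baseline. The share falling by more than 5% is Φ((−0.05 × z + 0.10) / 0.20).

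- z = 2.0: Φ(0) = 50.0%
- z = 3.0: Φ(−0.05/0.20) = Φ(−0.25) = 40.1%
- z = 3.5: Φ(−0.075/0.20) = Φ(−0.375) = 35.4%

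Those gaps of 1.0 to 1.5 z are plausible between individual children. For clinics, take assumed means of 2.3 and 2.6 and treat each clinic as if all its children were at the mean:

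- z = 2.3: Φ(−0.015/0.20) = Φ(−0.075) = 47.0%
- z = 2.6: Φ(−0.030/0.20) = Φ(−0.15) = 44.0%

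The difference is 3 percentage points.

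**4. Sensitivity to the SD.**

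| Assumed SD | z = 2.0 vs 3.0 | z = 2.3 vs 2.6 |
|---|---|---|
| 0.15 | 50.0% vs Φ(−0.333) = 36.9% | Φ(−0.10) = 46.0% vs Φ(−0.20) = 42.1% |
| 0.20 | 50.0% vs 40.1% | 47.0% vs 44.0% |
| 0.25 | 50.0% vs Φ(−0.20) = 42.1% | Φ(−0.06) = 47.6% vs Φ(−0.12) = 45.2% |

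The artefact is about 8 to 13 points for a gap of 1.0 z and about 2 to 4 points for a gap of 0.3 z.

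**5. Same check with a fixed cut.** With a required fall of d z-score units for every child, the share is Φ((−d + 0.10) / 0.20), which does not contain baseline z. Under the same assumptions the artefact disappears.

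**The case against.** The strongest reply has four parts.

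- *Direction is a wording gap.* In a weight-management audit that judges effectiveness, an analyst would naturally read a reduction of more than 5%, which places gainers correctly with children who did not improve. This largely stands. A reader might infer that gainers will be counted as successes, but the text only permits that reading and does not require it.
- *The category is not the main result.* The primary objective concerns acceptability, reach, participation and retention. Clinical effectiveness is secondary, BMI z-score change is also analysed as a continuous variable, and the economic evaluation in Part 5 uses cost per unit of BMI z-score. Neither the direction defect nor the percentage defect touches those analyses. This stands and limits the severity.
- *Case mix between clinics is not documented.* A reader might infer that the tertiary clinic treats more severe cases than the secondary clinics, and so a distortion of 10 to 15 points. The documents do not support that. The Background contrasts secondary and tertiary services together with primary care and does not rank the two against each other, and no clinic-level severity is given. Gaps of 1.0 to 1.5 z between clinic means have no support in the text.
- *Modelling could absorb it.* The Data analysis section plans to model predictors of effectiveness, and its list is not exhaustive, so baseline z could be added. That would help the modelled comparison, but not the plain category rates, and baseline z is not named.

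A reader might also want to argue that z-scores compress at very high BMI. The article names no growth reference, so the size cannot be worked out from it, and any such compression would affect the continuous change as well. It is not a defect of this category in particular.

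The baseline-dependent bar remains: it follows from the stated rule by arithmetic alone and survives the most favourable reading of the direction.

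**Conclusion.** The point holds at moderate severity. The category is fixed in the article without a direction, and its percentage-of-z form makes the required change grow with baseline severity, from 0.075 at z = 1.5 to 0.175 at z = 3.5. This is more than detail left to an analysis plan, because the cut-off itself is stated.

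How far it would distort the comparison depends on how far the models of care differ in baseline z, which the article does not give. With an assumed change of mean −0.10 and SD 0.20, the spurious difference is about 10 points for a gap of 1.0 z and about 3 points for a gap of 0.3 z. The article does not support concluding that the effectiveness comparison as a whole is invalid, since the continuous analysis is unaffected by these two defects.

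**What to change.** In the Part 4 Data analysis section:

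1. Replace the percentage-of-z category with a signed, fixed reduction in BMI z-score: a reduction of at least a stated amount against not. State the amount and its justification before the outcome data are examined. The article offers no value, so the trial team must choose it.
2. Show increases of at least the same amount as a separate row, so that gainers are visible.
3. Name baseline BMI z-score as a covariate in the model that compares models of care.
4. Optionally, add relative change in BMI as a percentage of the age- and sex-specific 95th centile as a supplementary measure for children with severe obesity. State that the change is relative and not in percentage points.

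Keep the continuous change in BMI z-score as it is. Height and weight are already collected at baseline, three and six months, so this costs wording only. The downside is slightly less comparability with reports that use percentage change in z. If the present category is kept for that purpose, it should at least state that a reduction is meant and that baseline z is the denominator, and be labelled as dependent on baseline severity.

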### Part 5: Economic evaluation of each model of Care for Pediatric Weight management services

Part 5 will address the following objective:

Secondary objective: Determine the costs and cost-effectiveness of the different models of care from a health provider and consumer perspective.

We will determine the costs and cost-effectiveness of weight management services from the perspective of the health care provider and patients and their families. We will consider not only the cost of setting up services for child weight management in each of the participating LHDs, but also any out-of-pocket costs borne by patients and their families. Health system costs will include fixed and variable costs including clinic set up, staffing costs based on staff full time equivalents, consumables and materials purchased for the running of the clinics. We will use standard techniques to consider overhead costs based on square meters of space occupied within existing hospital or clinic premises. These costs will primarily be based on financial records from LHDs. Additionally, there will be ongoing healthcare costs (e.g. general practitioner, specialist and tertiary services) as each child moves through the care pathway – these will include health system and out-of-pocket costs to patients.

#### Participants

As part of the questionnaire developed for Part 1 of the study (consented) parents/carers will be asked about their time inputs as they navigate the care pathway e.g. time to attend consultations and travel time, type of services used, including specialist services and use of organised programs.

#### Quantitative

Participant costs will include any out-of-pocket costs for referrals, and treatment plus productivity costs relating to missed work. Participant and family costs will be important in assessing the equity and reach of the programs and may impact on the acceptability of different models of care. In addition, we will determine health system costs using standard costs for consults. Hence, for each LHD we will be able to estimate the mean cost per child using the service and total set-up costs required for expansion into other LHDs.

#### Data analysis

The primary outcome for the economic evaluation will be incremental cost per unit BMI z-score avoided in the new model of care compared with the existing model of care. Incremental cost-effectiveness ratios (ICERs) will be determined for each model of care, in each LHD.

## Discussion

This is a unique time in NSW, Australia when several health services are currently working collaboratively with the aim of implementing secondary level care of child weight management in an integrated fashion. However, the models of care to be implemented differ based on the varying level staffing and intensity of the intervention. There have been no studies examining the cost, impact, appropriateness and acceptability of various integrated child and family-focused clinical models of care in secondary and tertiary PWMS within Australia. The current or planned clinical services are all based on the same broad principles of clinical management of pediatric obesity. However, it is important to test the clinical effectiveness of such models of care as the intensity, cost and cost-effectiveness is likely to differ based on the model used.

Results from the study will enable recommendations for future service planning to optimise scalability and sustainability of integrated, responsive and effective care of pediatric patients with overweight or obesity. This study will help to generate an evidence base for secondary and tertiary level weight management models of care in participating LHDs.

The findings from this project will feed directly in to the NSW Premier’s Priority work on “Tackling Childhood Obesity”. The project will improve the design and delivery of local services for children and their families, by enhancing the accessibility, acceptability, reach and impact of services for children and families from diverse regions of NSW. Results from this study will assist in examining ways to better integrate secondary and tertiary pediatric weight management with primary care management and existing community-based programs. As a result, health service managers and senior clinicians will be better informed about the types of models of care and health care pathways that may work best in their region or health service. Such information is required to inform long-term sustainability and scalability of secondary and tertiary care services to the large number of families with children above a healthy weight. Further, children and adolescents affected by obesity will have improved access to secondary level treatment services, which are currently very limited.

## Abbreviations

BMI: Body Mass Index
LHD: Local Health District
NSW: New South Wales
PWMS: pediatric weight management service(s)
